## Abstract

**Introduction:**

Demand for colonoscopies and CT colonography (CTC) is exceeding capacity in National Health Service Trusts. In many patients colonoscopies and CTCs show no significant bowel disease (SBD). Faecal Immunochemical Testing (FIT) is being introduced to prioritise patients for colonoscopies but is insufficient to identify non-SBD patients meaning colonoscopy and CTC demand remains high. The REducing Colonoscopies in patients without significant bowEl DiseasE (RECEDE) study aims to test urine volatile organic compound (VOC) analysis alongside FIT to improve detection of SBD and to reduce the number of colonoscopies and CTCs.

**Methods and analysis:**

This is a multicentre, prospective diagnostic accuracy study evaluating whether stool FIT plus urine VOC compared with stool FIT alone improves detection of SBD in patients referred for colonoscopy or CTC due to persistent lower gastrointestinal symptoms. To ensure SBD is not missed, the dual test requires a high sensitivity, set at 97% with 95% CI width of 5%. Our assumption is that to achieve this sensitivity requires 200 participants with SBD. Further assuming 19% of all participants will have SBD and 55% of all participants will return both stool and urine samples we will recruit 1915 participants. The thresholds for FIT and VOC results diagnosing SBD have been pre-set. If either FIT or VOC exceeds the respective threshold, the participant will be classed as having suspected SBD. As an exploratory analysis we will be testing different thresholds. The reference comparator will be a complete colonoscopy or CTC. Secondary outcomes will look at optimising the FIT and VOC thresholds for SBD detection. An economic evaluation, using a denovo decision analytic model, will be carried out determine the costs, benefits and overall cost-effectiveness of FIT +VOC vs FIT followed by colonoscopy.

**Ethics and dissemination:**

Ethical approval was obtained by Liverpool Central Research Ethics Committee (20/NW/0346).

**Trial registration number:**

RECEDE is registered on Clinicaltrials.gov NCT04516785 & ISRCTN14982373. This protocol was written and published before results of the trial were available.

Strengths and limitations of this studySimple observational trial design that does not affect the standard care of participants.The study can be conducted entirely remotely.Reliance on patients collecting their samples at home and posting/bringing their samples back to the hospital may result in a higher proportion of missed samples as there is a greater chance of patients forgetting.Recruitment rate is dependent on COVID-19 19 as referral rates drop when COVID-19 19 cases are high.^4^

## Introduction

There is currently a disparity between demand and available resources for colonoscopies and CT colonography (CTCs) within the National Health Service (NHS). Before the COVID-19 pandemic, around 300 000 patients were being referred annually to NHS trusts suspected of having colorectal cancer (CRC) and this number was rising.^1^ Most patients referred with suspected CRC are offered an invasive colonoscopy or CTC examination, but only 30% of these participants have significant bowel disease (SBD).^2^ SBD is defined as CRC, adenomatous polyps or inflammatory bowel disease (IBD).^3^ The remaining 70% have a normal examination with 30% of those having functional conditions such as irritable bowel syndrome (IBS).

Set against this there will remain a capacity shortfall for colonoscopies and CTCs for the foreseeable future. This limits capacity of the NHS to extend CRC detection within the Bowel Cancer Screening Programme (BCSP) or to investigate those who present through the emergency department. The imbalance between capacity and demand, coupled with a lack of an accurate triage test makes it difficult for the NHS to stratify patients who present with bowel symptoms to those most at risk of SBD. In the COVID-19 era, faecal immunochemical testing (FIT) is being introduced to triage patients who present with lower gastrointestinal (GI) symptoms.^4^ However, almost all patients still receive a colonoscopy or alternative colonic imaging at some time and the optimum threshold for FIT has yet to be determined. The National Institute for Health and Care Excellence (NICE) have recommended 10
μ
gHb/g faeces,^5^ whereas the BCSP have set a cut-off of 120
μ
gHb/g faeces.^6^ Even at the lower threshold some SBD cases can be missed.^2 7 8^ Previous data have shown that FIT alone (at a threshold of 7
μ
gHb/g faeces) has a sensitivity of 80%, 53% and 86% for CRC, adenomatous polyps and IBD respectively.^2^ A lower FIT threshold may reduce the number of false negatives but it will increase the number of unnecessary colonoscopies and CTCs in patients with no abnormalities (false positives). Moreover it will always miss cases of SBD where there is no bleeding, and a high proportion of malignant tumours never bleed.

Thus, this study will test urine volatile organic compound (VOC) analysis alongside FIT to improve detection of SBD. VOCs are produced by metabolic responses to inflammation in the presence of illness, therefore they are disease specific.^9–11^ Previous work has identified key metabolites in inflammatory GI disease^12^ and, on its own, VOC analysis has a sensitivity of 80%, 92% and 86% for CRC, adenomatous polyps and IBD, respectively.^13 14^ When FIT and VOC are used in combination (FIT followed by VOC in the FIT negative), sensitivity of CRC improves from 80% to 97%, which is similar to the results of colonoscopy and CTC.^13 15^ Existing studies have already demonstrated the utility of VOC analysis in detecting IBD, coeliac disease and bile acid diarrhoea while also being negative in functional conditions such as IBS.^16 17^ Many patients with slightly raised FIT are found to have no SBD and we will examine the value of VOC in this group to see if a negative VOC can rule out SBD.

Therefore, the objective of this study is to investigate whether the combination of FIT and VOC analysis compared with FIT alone improves detection of SBD in patients who present with lower GI symptoms. This could be by both improving sensitivity in patients with FIT <10 and but also possibly by improving specificity in patients with slightly raised FIT but negative VOC. If correct, fewer patients will be referred for colonoscopies and CTCs, freeing up capacity and reducing NHS costs, while reducing disutility in patients who do not benefit from an invasive examination. Within the COVID-19 era, this has added importance. If the proposed method of dual testing proves effective then not only will hospital capacity be improved but also fewer patients will be required to undergo colonoscopies or CTCs; streamlining the patient pathway and reducing the risk of viral transmission if colonoscopy generates aerosols.

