### Stool sample analysis

Stool samples will be analysed for traces of haemoglobin in the faeces using a HM-JACKarc. Participants samples will be defined as having suspected SBD if the value is >10
μ
 gHb/g faeces. Any previous FIT results collected to triage patients can be sourced from patient records if the test is <4 weeks before their colonoscopy or CTC.

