### Primary outcome analysis

The primary outcome is diagnostic accuracy (sensitivity, specificity, NPV and positive predictive value (PPV)) of the dual index test FIT and VOC analysis. The ‘or’ rule will be utilised for the primary analysis whereby a FIT result of >10 µgHb/g faeces OR a VOC result with predicted probability >0.63 implies that the participant is suspected of having SBD and needs to be referred for colonoscopy or CTC. We will report 2×2 tables of test accuracy of the dual test by the reference standard (final report from the colonoscopy examination and confirmatory histology report of SBD which is either colon cancer, colorectal adenomas or IBD), alongside summary measures of sensitivity, specificity, NPV and PPV, and their 95% CIs. These test accuracy estimates will be used in the economic model.

We will analyse the combined FIT+VOC test results as both parallel (results from both tests are interpreted in combination) and serial testing (VOC analysis only performed if FIT is negative). The ‘or’ rule will be considered in the interpretation of both parallel and serial tests where the diagnosis is positive when either test is positive, and negative when both results are negative. In the serial test, if the FIT is positive, then the diagnosis is positive. If FIT is negative we will use the result from VOC analysis and if that is positive then the diagnosis is positive. Mathematically, both methods should give the same diagnostic results but will make a difference in the economic model.

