### Secondary outcome analyses

Secondary outcomes include: ROC of FIT plus VOC to develop an optimum thresholds for SBD detection; sensitivity, specificity, PPV and NPV estimates and their corresponding 95% CI for each individual condition of SBD (CRC, colorectal adenomas and IBD) by each individual test and combination rules; compliance rates (return of samples); the types of SBD and microscopic colitis, and the number of cases missed by CTC, FIT and VOC analyses; potential number of avoidable colonoscopies and CTCs in patients without SBD; total NHS and personal social services costs and total quality of adjusted life years (QALY) associated with each option. To find the optimal thresholds of FIT and VOC we will first plot the ROC curves of both tests individually to find the individual optimal thresholds (the one that gives the greatest specificity while achieving 97% sensitivity). Second, we will plot combinations of the two tests in the ROC space and similarly, choose the combination of thresholds which has greatest specificity while achieving the required 97% sensitivity to avoid colonoscopy. The combined thresholds of FIT and VOC in the ROC space are calculated by combining every unit of FIT (from 10 to 120µgHb/g faeces) with every unit of the predicted probability of VOC (from 0.63 to 1). Both the ‘or’ and ‘and’ rules will be explored when combining the FIT and VOC results to define a case as either SBD positive or SBD negative. If both tests are in discordant then the diagnosis is negative. For each of the thresholds that we derive from the ROC curves, we will also report the NPV estimates. This will produce an overestimate of test accuracy, which we will use as a sensitivity analysis in the economic model, as a more optimistic assumption to demonstrate the range of uncertainty.

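### The primary *or* rule cannot reduce referrals against FIT alone, and the exploratory threshold grid is poorly placed to test the specificity aim at 97% sensitivity

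*Protocol article*

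**What the plan says.** The Introduction of the protocol article sets the comparison as FIT plus VOC against FIT alone and gives two routes to benefit. One is better sensitivity when FIT is below 10. The other, offered only as a possibility, is "improving specificity in patients with slightly raised FIT but negative VOC". Of participants with slightly raised FIT it says "we will examine the value of VOC in this group to see if a negative VOC can rule out SBD". It then concludes: "If correct, fewer patients will be referred for colonoscopies and CTCs, freeing up capacity and reducing NHS costs".

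Under Stool sample analysis, FIT alone is read at one cut-off: "Participants samples will be defined as having suspected SBD if the value is >10". Under Primary outcome analysis, a FIT above that same value or a VOC predicted probability above 0.63 "implies that the participant is suspected of having SBD and needs to be referred for colonoscopy or CTC". The serial version also ends at positive as soon as FIT is positive.

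Under Secondary outcome analyses, FIT cut-offs from 10 to 120 are combined "with every unit of the predicted probability of VOC (from 0.63 to 1"), under both *or* and *and* rules. The chosen combination is the one with the greatest specificity among those that reach 97% sensitivity.

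**The concern.** The objective names a comparator and an expected consequence, and the primary rule rules that consequence out against that comparator. A participant with slightly raised FIT and negative VOC, the person in whom VOC is meant to spare an examination, is always referred under the primary rule.

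That leaves the secondary search to carry the specificity aim. Its starting corner is the primary rule, and both axes only rise from there, so sensitivity can only be given up. The floor is the same 97% that the primary rule is planned to have. Two things are at stake. A reader could take the primary result as evidence about referrals saved against FIT alone. And the search could return no rule, or one whose true sensitivity lies below the floor that it appears to meet.

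**Working it through.** **1. The plan's own figures.** Inputs from Sample size calculation: sensitivity 97%, 200 SBD cases, prevalence 19%, return rate 55%. The Zhou-Li interval at 0.97 with n = 200 runs from 0.939 to 0.988, a width of 0.049 against the stated 5%. 200/0.19 = 1052.6, so 1053. 1053/0.55 = 1914.5, so 1915. All reproduce. The 97% comes from CRC in the earlier study and is applied here to SBD as a whole.

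**2. Primary rule against FIT alone.** Four cells cover all participants (t is a FIT cut-off above 10):

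| Cell | FIT alone, >10 | Primary *or* | *or* with FIT cut-off t | *and* at 10/0.63 |
|---|---|---|---|---|
| A: FIT >10, VOC >0.63 | + | + | + | + |
| B: FIT >10, VOC ≤0.63 | + | + | − if FIT ≤ t | − |
| C: FIT ≤10, VOC >0.63 | − | + | + | − |
| D: FIT ≤10, VOC ≤0.63 | − | − | − | − |

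(The fourth column has the VOC cut-off at 0.63.)

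Change in referrals against FIT alone:
- Primary *or*: +n(C), never negative. Specificity changes by −P(C | no SBD), never positive. Nobody in cell B is reclassified.
- *or* with FIT cut-off t and VOC cut-off v: +n(FIT ≤10, VOC >v) − n(10 < FIT ≤ t, VOC ≤ v). This can take either sign.
- *and* at 10/0.63: −n(B), never positive.

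**3. Does the secondary grid reach cell B?** Yes. FIT 10–120 gives 111 values, and VOC 0.63–1 in steps of 0.01 (step assumed) gives 38, so 111 × 38 = 4218 *or* points. Of these, 110 × 38 = 4180 have a FIT cut-off above 10 and score at least part of cell B as negative. The *and* rule does so throughout.

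**4. What the 97% floor allows.** Raising either cut-off under *or* can only remove positives, so no *or* point is more sensitive than the 10/0.63 corner. The Introduction gives FIT sensitivities of 80%, 53% and 86% (CRC, adenoma, IBD, at a cut-off of 7) and VOC sensitivities of 80%, 92% and 86%. If the tests are independent given disease, *or* sensitivity at the corner is 1 − (1 − SeF)(1 − SeV):
- CRC: 1 − 0.20 × 0.20 = 96.0%
- Adenoma: 1 − 0.47 × 0.08 = 96.2%
- IBD: 1 − 0.14 × 0.14 = 98.0%

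The *and* rule cannot exceed FIT alone: at most 80%, 53% and 86% at a cut-off of 7, and no higher at >10. On these inputs it cannot meet 97%.

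**5. Chance that any point qualifies.** The floor is 0.97 × 200 = 194 detected cases. Because the corner is the most sensitive point, some point qualifies only if the corner does. With X ~ Bin(200, true sensitivity at the corner):

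| True sensitivity | P(X ≥ 194) | No qualifying point | P(X ≥ 195), room to lose a case |
|---|---|---|---|
| 96% | 0.31 | 0.69 | 0.19 |
| 97% | 0.61 | 0.39 | 0.44 |
| 98% | 0.89 | 0.11 | 0.79 |

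This step needs no assumption about specificity or dependence.

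**6. What is selected when a point qualifies.** Simulation with 200 SBD and 1053 − 200 = 853 non-SBD participants. Assumed sensitivity/specificity: FIT 70/80 at 10, VOC 90/65 at 0.63, independent given disease, so the corner is 1 − 0.30 × 0.10 = 97%. FIT was log-normal and VOC logit-normal, with spreads varied because the article gives none. About 39–43% of studies had no qualifying point. In the others the selected rule had a true sensitivity of about 95%. A FIT cut-off above 10 was selected in 39–50% of all studies. With the VOC grid extended below 0.63, the no-solution outcome disappeared. That is expected, since a low enough VOC cut-off makes nearly everyone positive.

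**The case against.** A reader might infer that the specificity aim cannot be answered at all, or that the grid has no slack. The document does not support either reading. Step 3 shows that the grid scores slightly raised FIT with negative VOC as negative at most *or* points and at every *and* point, so accuracy there can be estimated. Raising the FIT cut-off costs a case only if an SBD patient lies in the raised band and is also VOC-negative, and the simulation often selected a FIT cut-off above 10. If true sensitivity exceeds 97%, there is more room. This part of the objection stands.

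Fewer referrals can also be read against current practice. The article says that almost all patients still get colonic imaging, enrols only people already judged to need it, and plans to count avoidable examinations in patients without SBD. Against that baseline the claim is possible under the primary rule. But the objective, the study design and the economic evaluation all name FIT alone as comparator, and the claim follows the objective directly. The text needs to say which baseline is meant.

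The specificity route is hedged as a possibility, and the article itself calls the searched thresholds an overestimate, used as an optimistic input to the economic model. Both points are fair and make this less serious. They do not remove the conflict with the primary rule, nor the upward-only grid, which this article fixes rather than leaving to the SAP. The exact FIT band for a subgroup table could properly sit in the SAP.

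**Conclusion.** Wrong as written on referrals: under the primary rule, fewer referrals than with FIT alone is impossible by set inclusion, with no assumption beyond a common FIT cut-off. The claim can hold only against colonoscopy or CTC for all. The number of extra referrals is the count with FIT ≤10 and VOC >0.63. The article gives no specificities from which to predict it, so no figure is put on it here.

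The specificity aim can be estimated, but only through an exploratory search that is badly set up for it. At a true primary sensitivity of 97%, the chance of no qualifying rule is about 39% from the binomial and 39–43% by simulation. It falls to 0.11 at a true 98% and rises to 0.69 at 96%. The true sensitivity of about 95% for the selected rule rests on the assumed accuracies, conditional independence and distribution shapes in step 6.

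**What to change.** 1. State that against FIT alone at the same cut-off the primary *or* rule accepts extra referrals in exchange for sensitivity, and tie the expectation of fewer referrals to colonoscopy or CTC for all.
2. Extend the exploratory VOC grid below 0.63, so that a higher FIT cut-off can be offset by a lower VOC cut-off and a point meeting 97% exists.
3. Report, as a labelled secondary analysis, SBD risk with 95% CI in VOC-negative participants within a FIT band just above 10. Fix the band's upper limit before index and reference results are linked. Give referrals avoided and SBD missed against FIT alone.

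Cost: changes to protocol and SAP wording, slightly more computation and one extra table, with no new data. The headline claim becomes narrower. The larger search remains optimistic and should keep that label.

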## Methods and analysis

### Study design and procedures

This is a multicentre (UK only), prospective diagnostic accuracy study, sponsored by the University Hospitals Coventry & Warwickshire (UHCW) to compare dual testing of stool FIT plus urine VOC markers compared with stool FIT alone in the detection of SBD. Participants will be recruited when referred to secondary care for investigation of lower bowel symptoms, after informed consent is received. Inclusion criteria will be: patients referred non-urgently or urgently (fulfilling the national criteria for referral—NICE NG12)^18^ with lower GI symptoms and determined by the overseeing clinician to require colonoscopy or CTC; minimum age of 18; able to provide informed consent, and have the ability to return both stool and urine samples. Exclusion criteria are those who are pregnant. Participants will be recruited over the phone or face-to-face during a clinic visit which precedes their colonoscopy or CTC. Participants will be asked to provide a stool sample and urine sample at least 24 hours before commencing their bowel cleansing medication. Stool samples will be collected at home by the participants using FIT collection kits and posted directly to the analysis site. If the participant has already completed a FIT during their referral pathway, we will use this data if the time between the FIT and their colonoscopy is less than 4 weeks, otherwise we will request that the participant to provide another FIT. Urine samples will be returned to hospitals and frozen at −80°C pending future analysis. Urine samples can either be collected during a clinic visit that precedes their colonoscopy or CTC, or collected at the home of the participant and brought back by the participant. We will aim for the time between the urine sample being produced and the urine sample being frozen at −80°C to be less than 4 hours, otherwise we will ask participants to freeze their urine samples in their home freezer. For the purposes of the economic analysis, a subset of participants (20% of total) undergoing colonoscopy or CTC will also be asked to complete questionnaires at five time points surrounding their examination. This will help determine the disutility and costs associated with undergoing colonoscopy or CTC, which will be used as inputs in the economic model (see section Economic Evaluation below). Figure 1 shows a participant flow diagram once enrolled in the REducing Colonoscopies in patients without significant bowEl DiseasE (RECEDE) study.

**Figure 1 F1:**
[figure not shown]
Participant flow diagram for RECEDE. *Indicates that the data is only being collected in 20% of participants. CTC, CT colonography; EQ-5D-5L, EuroQol-5 Dimension-5 Level; GI, gastrointestinal; RECEDE, REducing Colonoscopies in patients without significant bowEl DiseasE.

### Sample size calculation

To replace colonoscopy—the current gold standard for diagnosing bowel conditions—and/or CTC, FIT and VOC analysis requires a very high sensitivity to avoid false negatives. High specificity is also desirable, to reduce false positives. Based on our previous study, the sensitivity of FIT and VOC analysis to detect CRC was 97%, comparable to colonoscopy. Therefore, the sample size was determined to achieve a sensitivity of at least 97% with a 95% CI width of 5% (Zhou-Li method^19^ as described in box 1). The required number of participants with SBD to achieve this sensitivity is 200. Figure 2 shows CIs for different observed sensitivity cases of SBD (150, 200, 250). Figure 3 shows the widths of the CI limits are narrower and wider when the observed sensitivity is above or below 97%,^13^ respectively. This sample size is also robust to negative predictive value (NPV), an outcome that is of interest as a high NPV suggests that participants without SBD would avoid having colonoscopy examination. Assuming the prevalence of SBD in the study population is 19%, then 1053 participants are required. Based on our previous study,^13^ the return rate of both stool and urine samples that are eligible for analysis is about 55% resulting in a total required sample size of 1915 participants across multiple UK sites within a 24-month period.

Box 1Sample size determination based on CI methodThe Zhou Li CI is 
$\left(\frac{e^{LL}}{1+e^{LL}},\frac{e^{UL}}{1+e^{UL}}\right)\left(\frac{e^{LL}}{1+e^{LL}},\frac{e^{UL}}{1+e^{UL}}\right)$
 where 
$LL=ln\left(\frac{\bar{S}\bar{e}}{1-\hat{Se}}\right)-\frac{1}{\sqrt{n\hat{Se}(1-\hat{Se})}}g^{-1}(z_{1-\alpha /2})$
, 
$UL=ln\left(\frac{\bar{S}\bar{e}}{1-\hat{Se}}\right)-\frac{1}{\sqrt{n\hat{Se}(1-\hat{Se})}}g^{-1}(z_{\alpha /2})$
, 
$g^{-1}(x)=-\sqrt{n}\left(\frac{6}{\hat{\gamma }}\right)\left\{{\left[1-\frac{\hat{\gamma }}{2}\left(\frac{x}{\sqrt{n}}-\frac{\hat{\gamma }}{6n}\right)\right]}^{1/3}-1\right\}$
and
$\hat{\gamma }=\frac{1-2\bar{S\bar{e}}}{\hat{Se}(1-\hat{Se})}$

